### Inclusion criteria

21-years and older.Meet the definition of postconcussion syndrome as defined by Tator et al. (2016), which requires a participant to report any 3 symptoms or more (from an inclusive list of the 40 most commonly reported persisting symptoms) lasting at least 1-month following the diagnosis of a concussion [13]. Concussion was defined according to the 6th International Consensus Statement on Concussion in Sport [10].Have adequate language skills in English to read and take part in rehabilitation treatment programs.Demonstrate an objective impairment on the baseline standardized exam, placing the participant into one of the three subgroups (autonomic, cervical or vestibulo-ocular).

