### Randomization and masking

We will use simple randomization to allocate participants to one of two sequences of interventions: Group A: personalized care program followed by active control; or Group B: active control followed by personalized care program. The study coordinator (NM) conducted the randomization using a randomized table generator (GraphPad Software Inc, La Jolla, CA). Randomization will be concealed; no other study personnel will be aware of the intervention assignments. However, it was not possible to blind the study coordinator (NM) as they are one of the main treating clinicians. Additionally, it was not possible to ensure adequate blinding of the participants, given the necessary thorough description of the treatment procedures that occurred during the informed consent process.

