### Assessments / procedures

Participants will undergo a comprehensive clinical evaluation at the KITE Innovations and Rehabilitation Clinics or at the Pain and Wellness Centre to differentiate their post-concussive subgroup(s) [7]. Evaluation will consist of recommended elements of a standardized clinical physical examination outlined by Matuszak et al. (2016) [14]. Specifically, the study coordinator (NM) will perform all components of the examination including a neurological exam consisting of cranial nerve screen, motor testing of the upper and lower extremities and deep tendon reflexes; a musculoskeletal examination assessing for tenderness over the head and neck, range of motion of the cervical spine and Spurling test; joint position sense error test (JPSE) of the cervical spine in flexion, extension, lateral flexion and rotation, which has shown to be a reliable and relevant measure to distinguish normal and neck pain patients [15–17]; balance/coordination examination assessing static and dynamic balance via the Balance Error Scoring System (BESS), and tandem walking with eyes open and closed [18]. The BESS consists of three static stances performed on both a firm and foam surface. The BESS has been shown to have moderate to good reliability in assessing static balance as well as has been shown to detect balance deficits in participants with concussion [19]. Continuing, a vestibular-ocular examination consisting of evaluation of the eyes in eight positions, evaluating nystagmus, saccades, smooth pursuit and near point convergence/accommodation. Additional tests will be included if dizziness or imbalance are present and will include: orthostatic vital signs via supine-to-stand stress test; Dix-Hallpike maneuver and assessment of dynamic visual acuity [20].

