### Intervention

The study coordinator (NM) will perform all components of the listed assessments/procedures. The interventions will be delivered by advanced-trained chiropractors at the Pain and Wellness Centre and the study coordinator (NM) at the KITE Innovations and Rehabilitation Clinics.

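### The protocol claims concealed randomisation, but the procedure described does not secure it: the coordinator who ran the randomisation also performs the examination that decides eligibility, and treats participants

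*Protocol article*

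**What the plan says.** All references are to the Methods of the protocol article.

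- **Randomization and masking.** Allocation is by simple randomisation to one of two sequences. The study coordinator "conducted the randomization using a randomized table generator". The concealment claim is "Randomization will be concealed; no other study personnel will be aware of the intervention assignments". The section then says the coordinator could not be blinded, "as they are one of the main treating clinicians", and that participants could not be adequately blinded either.
- **Inclusion criteria.** A participant must "Demonstrate an objective impairment on the baseline standardized exam, placing the participant into one of the three subgroups". Under Exclusion criteria, an examination without positive physical findings rules the person out.
- **Assessments / procedures.** The coordinator "will perform all components of the examination including a neurological exam", and the Intervention section repeats that the coordinator "will perform all components of the listed assessments/procedures".
- **Intervention.** "The interventions will be delivered by advanced-trained chiropractors at the Pain and Wellness Centre and the study coordinator" at the other clinic.
- **Study design.** Randomisation comes after the examination, RPQ, EEG, Neck Disability Index and PHQ-9. Everyone crosses over at week 6, without washout.

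**The concern.** Allocation concealment is distinct from blinding. It requires that the person deciding whether a candidate enters cannot know, or work out, the next assignment. The article hides assignments from everyone except the coordinator, and the coordinator is the person whose findings decide entry. If the coordinator can see the next assignment, a borderline finding can be read one way or the other, or an enrolment delayed, depending on which sequence comes next. This need not be deliberate.

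Concealment matters more than usual in this trial. Participants know their programme, the primary outcome is self-reported, and a main treating clinician runs the randomisation. Those features are disclosed and are not the complaint. They do leave concealed allocation as the main remaining protection for the comparability of the two sequences at entry. A difference created by selection at entry cannot be reliably removed in the analysis, because what drove the selection may not have been recorded.

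**Working it through.** The plan gives no figure for this point, so the check sets the stated roles side by side.

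**1. Who does what**

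| Function | Person named | Section |
|---|---|---|
| Runs the randomisation | Coordinator | Randomization and masking |
| Performs the examination | Coordinator, all components | Assessments / procedures; Intervention |
| Decides entry | The result of that examination | Inclusion and Exclusion criteria |
| Treats | Coordinator at one clinic, chiropractors at the other | Intervention |
| Exempt from concealment | Coordinator | Randomization and masking |

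The first three functions rest with one person, who is also the one exempted. No one independent is named as making or keeping the sequence.

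**2. Does the examination leave room for judgement?** Partly. Under Assessments / procedures, the treadmill criterion has a numeric element: a symptom rise of three or more points on a 0–10 scale. The cervical screen rests on range of motion with palpated joint restriction and pain, on trigger points, or on joint position testing. The vestibulo-ocular screen rests on an oculomotor screen or on balance testing. Palpation in particular is the examiner's reading. A positive finding in one domain is enough for entry, so a candidate whose only finding is cervical could be admitted or turned away on that reading.

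**3. Does the stated order close the gap?** Not by itself. Study design puts randomisation after the examination and baseline measures. That helps only if the next assignment is unknown to the examiner until those are recorded. The article does not secure this when the examiner also runs the randomisation. Table 1 also marks eligibility under both the enrolment and the allocation columns, so the order is not watertight.

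**4. Is the claim about other personnel tenable?** Not after allocation. Chiropractors deliver the programmes at the Pain and Wellness Centre and must know which one they are giving.

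**5. Which comparisons are exposed?** Statistical analysis plans a group-by-time analysis of variance, an analysis of covariance and unpaired t-tests. Comparisons between sequences, including the first-period comparison at week 6, depend on the sequences being comparable at entry. Contrasts within a person depend on it less.

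**6. Illustration of sensitivity, not an estimate.** Assume no true effect, 25 per group (half of the planned 50), a two-sided 5% test of the week-6 RPQ-13 means, and a shift *b* between groups caused by selection. The article states no SD. An SD of about 10 is roughly what the planned 50 participants and the 8-point difference imply at 80% power: the detectable standardised difference with 25 per group is 0.809, and 8 / 0.809 = 9.9. SDs of 8 and 14 are shown as a range.

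SE = SD × √(2/25). Type I error = Φ(−1.96 − b/SE) + 1 − Φ(1.96 − b/SE).

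For SD 10, SE = 2.83. With b = 2, b/SE = 0.707, and the error is Φ(−2.667) + 1 − Φ(1.253) = 0.004 + 0.105 = 0.109.

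| Shift b (points) | SD 8 | SD 10 | SD 14 |
|---|---|---|---|
| 0 | 0.050 | 0.050 | 0.050 |
| 1 | 0.073 | 0.064 | 0.057 |
| 2 | 0.143 | 0.109 | 0.080 |
| 3 | 0.264 | 0.186 | 0.118 |
| 4 | 0.424 | 0.293 | 0.173 |

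Nothing in the documents says which row applies, or whether the shift is other than zero.

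**The case against.** The strongest defence is that the article does not say the coordinator holds a list of future assignments. It says only that the coordinator ran the randomisation with a generator. It also places randomisation after the baseline measures, and it condenses a full protocol that may describe custody. This stands in part. That the coordinator can see the next assignment is an inference, though a natural one when the coordinator runs the randomisation and nobody else is to know the assignments. It is why the conclusion is that the procedure described does not secure concealment, not that assignments were known. It does not rescue the claim, because the article itself states the roles and the exemption, and these are what conflict.

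A second defence is that the sentence about other personnel refers to the time before allocation, so the chiropractors' knowledge afterwards is loose wording. That is fair, and one clause would correct it.

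A third is that discretion is limited, because the treadmill criterion is partly numeric and every participant receives both programmes. Both facts narrow the exposure. Neither removes it from the cervical screen or from between-sequence comparisons.

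Two stronger readings may tempt a reader, and the documents support neither:

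- **Simple randomisation is itself a fault.** It is valid, and it is the least predictable scheme for anyone without the list. Chance imbalance in numbers is not bias. Stratified blocks are a trade-off, since in an open trial they can make later assignments easier to guess.
- **Imbalance between clinics would confound programme with therapist.** Each participant is treated at one clinic or the other, nothing suggests a change of clinic at crossover, and all receive both programmes. An imbalance would link sequence, not programme, to therapist.

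**Conclusion.** The concealment claim is wrong as written and should be corrected before it is relied on. The person who runs the randomisation also performs the partly judgement-based examination that decides eligibility, and treats participants. The only concealment stated is from other personnel, and that cannot last beyond allocation.

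The consequence is a possibility of selection bias in the first-period and between-sequence comparisons, with partial protection for within-person contrasts. Its size cannot be bounded from the documents, and the figures under the illustration rest on an assumed SD and assumed shifts. A reader might infer that participants were in fact steered into a sequence; nothing in the article shows that. Confidence is high on the conflict of roles, which is read directly from the text. That the coordinator has advance sight of assignments remains an inference.

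**What to change.** 1. Have the sequence generated and held outside the team that enrols, assesses and treats, for example in a randomisation module of an electronic data capture system or by an existing institutional statistician.
2. Release each assignment only after consent, eligibility, the examination and the baseline RPQ are recorded and locked.
3. Reword the concealment sentence to say who holds the sequence, that it is hidden from enrolling and assessing staff until release, and that treating clinicians know the assignment after allocation.
4. If participants have already been allocated, apply the new procedure to the remainder and report the procedure used until then as a limitation.

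Including site in the analysis model is an optional addition and is not needed for this point. Simple randomisation can stay.

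The cost is a short protocol amendment and the set-up of a randomisation module or an arrangement with a statistician. No extra visit, assessor or participant is needed.

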### Assessments / procedures

Participants will undergo a comprehensive clinical evaluation at the KITE Innovations and Rehabilitation Clinics or at the Pain and Wellness Centre to differentiate their post-concussive subgroup(s) [7]. Evaluation will consist of recommended elements of a standardized clinical physical examination outlined by Matuszak et al. (2016) [14]. Specifically, the study coordinator (NM) will perform all components of the examination including a neurological exam consisting of cranial nerve screen, motor testing of the upper and lower extremities and deep tendon reflexes; a musculoskeletal examination assessing for tenderness over the head and neck, range of motion of the cervical spine and Spurling test; joint position sense error test (JPSE) of the cervical spine in flexion, extension, lateral flexion and rotation, which has shown to be a reliable and relevant measure to distinguish normal and neck pain patients [15–17]; balance/coordination examination assessing static and dynamic balance via the Balance Error Scoring System (BESS), and tandem walking with eyes open and closed [18]. The BESS consists of three static stances performed on both a firm and foam surface. The BESS has been shown to have moderate to good reliability in assessing static balance as well as has been shown to detect balance deficits in participants with concussion [19]. Continuing, a vestibular-ocular examination consisting of evaluation of the eyes in eight positions, evaluating nystagmus, saccades, smooth pursuit and near point convergence/accommodation. Additional tests will be included if dizziness or imbalance are present and will include: orthostatic vital signs via supine-to-stand stress test; Dix-Hallpike maneuver and assessment of dynamic visual acuity [20].

Lastly, a physical exertion test will be performed via the Buffalo Concussion Treadmill Test (BCTT) protocol to specifically examine exercise intolerance. The BCTT is a well-established aerobic exercise test designed to assess exercise tolerance [21]. BCTT has shown clinical utility in identifying those likely to suffer persistent symptoms and the test is an excellent guide for exercise prescription following a concussion [22–24]. In addition to the baseline, 6-week and 12-week assessments, the BCTT will be performed weekly on participants in the personalized care stream who have been placed into the autonomic subgroup. This will be done to ensure proper advancement of their target heart rate participants are exerting themselves aerobically during training as rehabilitation and recovery progresses.

A positive or failed BCTT, placing the participant into the autonomic subgroup, will be defined as an inability to exercise at an age-appropriate heart rate threshold due to the exacerbation of concussion symptoms [15]. Exacerbation of symptoms will be defined as an increase of three points or more of their reported symptoms from baseline during exercise on an 11-point numerical rating scale (0–10). When patients can exert themselves and achieve near their age-appropriate maximum heart rate without exacerbation of symptoms, then the etiology or justification for persisting concussion symptoms will be ascribed to alternative problems [7].

A positive cervical spine screen, placing the participant into the cervical subgroup, will be defined as having an abnormal cervical spine range of motion with palpatory findings of facet joint restrictions and pain with supine facet joint motion palpation, cervical myofascial trigger points, or abnormal joint position error testing [14].

Finally, a positive vestibular or oculomotor screen, placing the participant into the vestibulo-ocular subgroup, will be defined as an abnormal vestibulo-oculomotor screen (VOMS) or abnormal static and dynamic balance testing as assessed via the Balance Error Scoring System and tandem walking, respectively [14].

As an additional element, participants’ cognition will be specifically examined through a rapid advanced quantitative electroencephalogram (EEG) via the NeuroCatch™ brain vital sign framework. Conventional EEG and event-related potentials (ERP) methods and analysis are time-consuming and typically restricted to controlled laboratory settings. This makes its use to help objectively guide a clinician’s management decision inaccessible to routine clinical use. Hajra et al. (2016) have detailed the framework of the brain vital sign in young and older individuals [25]. The framework translated well-established ERP responses into a portable, rapid, automated and easy-to-use evaluation method. It also incorporates a normative existing comparison framework analogous to existing vital sign metrics, such as that for blood pressure. Quantitative EEGs have repeatedly shown that concussions cause objective measurable changes in brain activity and therefore the functions of the structures from which they originate [26]. Specifically, Fickling et al., (2019) showed abnormal ERPs in elite male junior hockey players acutely following a concussion [27]. They also observed persistent impairments in ERP, specifically P300, at the time of return to play. Fickling et al. (2019) also found that players who did not sustain a concussion during the season still demonstrated abnormal ERPs (N400) at the end of the season, representing possible cognitive impairment as a result of cumulative subconcussive impacts [27]. Additionally, Ozen et al. (2013) demonstrated, in young adults who sustained a concussion a minimum 1-year before testing, a negative correlation between abnormal ERP (decreased amplitude of P300) and lingering impairments in cognitive processing, memory, and concentration [28]. NeuroCatch™ is a portable quantitative EEG and will be performed at the KITE Innovations and Rehabilitation Clinics. NeuroCatch™ acquires and reports on event-related potentials (ERPs) derived from electroencephalogram (EEG). As part of the brain vital sign framework, three ERPs (brain vital sign), auditory N100 (auditory sensation); auditory oddball P300 (basic attention); and auditory speech processing N400 (cognitive processing) will be evaluated.

### Intervention

The study coordinator (NM) will perform all components of the listed assessments/procedures. The interventions will be delivered by advanced-trained chiropractors at the Pain and Wellness Centre and the study coordinator (NM) at the KITE Innovations and Rehabilitation Clinics.

### Personalized care program

On the first therapy session, participants in the personalized care stream will be provided reassurance and psychoeducation via the bio-psycho-social model on understanding persistent symptoms consistent with usual care. Additionally, they will be afforded up to 12 treatments over the course of 6 weeks. The time frame of 6 weeks was selected given the treatment structure of prior clinical trials examining the effectiveness of physical interventions to address physical symptoms such as headaches, dizziness and neck pain [29]. Treatments will be standardized; however, given the heterogeneity of symptoms, components of the treatments will be personalized to the participants based on what subgroup they’re classified into at baseline. Personalized rehabilitative care differentiated by subgroups is outlined below:

**Autonomic group -** Participants will receive 60 min twice per week of supervised progressive sub-symptom aerobic exercise, as well as mindfulness-based training. As previously indicated, the target heart rate will be determined by the BCTT. This test will be done weekly to ensure the timely advancement of the target heart rate while participants’ rehabilitation and recovery progress. Participants will be instructed on various mindfulness-based techniques they can perform at home; however, in the clinic twice per week, a box-breathing technique will be utilized. Participants will be instructed to perform a minimum of 20 min of sub-symptom aerobic exercise as well as 20 min of mindfulness-based training daily outside the supervised exercise sessions.**Cervical group -** Participants will receive bi-weekly physical therapy to the cervical spine. Physical therapy will include soft tissue therapy directed to the cervical myofascial tissues and graded cervical spine facet mobilizations. Participants will also receive supervised 20 min of progressive neck isotonic strengthening exercises. Additionally, participants will be instructed to also perform daily 20 min of general neck stretches, range of motion exercises and neck strengthening exercises outside the supervised exercise sessions.**Vestibulo-Ocular group -** Patients will receive bi-weekly individualized oculomotor, vestibular and balance exercises including adaptation exercises, gaze stability exercises, visual-vestibular integration exercises, habituation exercises, and static and dynamic balance exercises. They will also be instructed to perform daily 20 min of individualized vestibular and oculomotor exercises based on their clinical exam outside the supervised exercise sessions.

In cases where participants are classified into more than one subgroup, they will receive the listed treatments provided to the sub-groups they are classified under. However, the frequency (twice per week) and duration (6-weeks) of care will not change regardless of subgroup determination.

Lastly, participants will be asked to refrain from seeking additional therapy; however, should they choose to undertake additional therapy outside of the trial they will be asked to document the modality and frequency of said therapy in the provided treatment adherence calendar that every participant receives at the start of the trial.

### Active control (usual care program)

All participants in the active control group will receive ‘usual care’, (one-hour session once a week for 6 weeks). The usual care model will consist of a single-hour session, provided at the first visit following the baseline assessment, devoted to reassurance and psychoeducation via the bio-psycho-social model on understanding persistent symptoms, including advice on adaptive illness behaviours, such as gradually resuming premorbid activities and avoiding excessive rest and “all-or-nothing behaviour”. Continuing, they will be educated on the fact that symptoms can be exacerbated not only with physical activity but also with extended cognitive load, which occurs commonly during working hours and social situations. As such they will be informed to take 5-10-minute breaks every hour if working and to find quiet spaces during busy social situations periodically. Additionally, as part of their weekly one-hour therapy sessions, participants will be afforded 30 min supervised symptom-limited aerobic exercise sessions. They will also be instructed to perform 20 min of symptom-limited aerobic exercise daily outside the supervised exercise sessions. Symptom-limited exercise will be defined as any form of aerobic exercise the participants will be able to perform without causing a greater than 2-point change in total symptoms as rated on an 11-point pain numerical rating scale (0–10) during their training. They will be instructed to rate their symptoms at rest before the exercise period and then exercise aerobically for 20 min without worsening their symptoms. They will be instructed to stop exercising and rest should their baseline resting symptoms exceed a 2-point increase during the exercise session. Additionally, when clinically indicated based on the standardized exam, participants will receive 20 min of general neck active range of motion exercises and stretching along with 20 min of generalized static and balance exercises. Participants will be advised to perform the neck and balance exercises two to three times per week outside of the supervised exercise sessions.

